**Methods/design:**

We are randomly assigning residents of long-term care facilities into one of three intervention groups: (1) *Usual Care Group* - individuals receive care as usual within their long-term care unit; (2) *Interpersonal Interaction Group* - individuals receive a comparable amount of one-on-one stationary interpersonal interaction time with study personnel administering the walking program; and, (3) *Walking Program Group* – individuals participate in a supervised, progressive walking program five days per week, for up to half an hour per day. Assessments completed at baseline, 2 and 4 months during intervention, and 2 and 4 months post-intervention include: gait parameters using the GAITRite® computerized system, grip strength, the Berg Balance Scale, the Senior Fitness Test, the Older Adult Resource Services Physical Activities of Daily Living, the Geriatric Depression Scale Short Form, the Cornell Scale for Depression in Dementia, the Revised Memory and Behavior Problems Checklist, the Short Portable Mental Status Questionnaire, the Coloured Analogue Scale, pain assessment scales, and the number and nature of falls. Sophisticated data analytic procedures taking into account both the longitudinal nature of the data and the potential for missing data points due to attrition, will be employed.

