### Sample size

Sample size calculations assumed a moderate standardized effect size of 0.40 [28], a small value for the intra-class correlation (i.e., the proportion of variation accounted for by LTC units) of 0.05, and α = .05, power = .80. Sample size calculations determined that a sample size of 129 total participants will provide ample power for repeated measures analyses [29]. A balanced design will be adopted, with equal numbers of participants in each group. We will collect data from an additional 50 participants in order to account for attrition due to refusal or inability to continue with the protocol. As well, morbidity and mortality may account for some attrition.

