### Procedures

After completing informed consent to participate in the study (or proxy consent by the appropriate SDM), all participants regardless of group will undergo a baseline assessment (see outcome measures section) conducted by trained study personnel prior to group allocation. Prior to enrolment in the specific study arm, family physicians are asked to optimize vitamin D levels, which will generally require obtaining vitamin D levels and prescribing 1,000 IU Vitamin D (if the participant is not already taking 1,000 IU or more) to control for potential influences on our study outcomes, and to be consistent with current recommendations [27]. Adherence with Vitamin D recommendations is monitored and reasons for intake problems are recorded.

Physical measures including respiratory rate, lying (after three to five minutes) and standing (after one minute) blood pressure, heart rate, as well as full height, knee-floor height, waist and calf circumference and weight are also collected at the beginning of the study, and except for height, measured also at week 8, week 16, week 24 and week 32, and whenever a medical concern arises. All adverse events (including falls, hospitalizations and surgeries) charted in nurses progress notes are collected, as are most recent full Resident Assessment Instrument-Minimum Data Set (RAI-MDS) and RAI-MDS updates, and the full, monthly medication administration record.

A licensed physiotherapist will assess the participant for fall risk and assign a visual analogue risk score ranging from negligible fall risk to highest fall risk, commenting on the reasons for the risk score assigned.

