### Other data collection

In order to control for confounding variables and to characterize the sample, the admission and most recent quarterly Resident Assessment Instrument-Minimum Data Set (RAI-MDS) [53] assessment data will be extracted. The RAI-MDS is a standardized LTC assessment tool designed to improve the care given to long-term care residents and it is used widely in Canada. The RAI-MDS data will be linked to the participants’ study ID number. The following RAI-MDS data will be included in the analysis: date of birth, race/ethnicity, gender, highest level of education, diagnoses on admittance, medications, health conditions; Cognitive Performance Scale; Depression Rating Scale; Index of Social Engagement; ADL Self-Performance Hierarchy Scale; Pain; Continence; Oral/Nutritional status; Communication; Mood and Behaviour Patterns; Physical Functioning and Structural problems; Activity Pursuit Patterns; Special Treatments and Procedures.

The incidence and nature of falls will be prospectively being collected using data from the Saskatoon Health Region Falls documentation protocol for the period of the intervention (four months) and for four months following intervention. Clinical staff records the nature and location of the fall, activity and symptoms at the time of the fall, and injuries resulting from the fall. Research assistants make copies of all falls records and add this to the research chart.

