### Data analysis

We hypothesize that participants taking part in the walking program will demonstrate maximal benefits compared to the no treatment control group (usual care) and the participants receiving only social interaction. We hypothesize that benefits of the walking program will include decreased fall rates, and improved balance, endurance, strength, mood, behaviour, activities of daily living and quality of life indices. As research has found that pleasant activities improve resident mood [54], we also hypothesize that participants in the social interaction group will demonstrate improvements in mood and other indices of quality of life.

The data will be analyzed using a random-effects multiple regression model [55]. The between-subjects factor will be condition (i.e., treatment and two control conditions). A random intercept for time (i.e., 5 measurement occasions) will be included to account for within-subject variation due to the repeated measurements. We will also evaluate model fit when a random slope for time is included in the model. Model fit will also be evaluated when the time x group interaction is included in the model. Additional covariates that may be included in the model are clinical measures from the RAI-MDS, such as the presence of comorbid conditions. Evaluation of model fit will be conducted using likelihood ratio tests and the Aikake Information Criterion [55]. Proportions of participants in the number of fall categories (e.g., non-faller, one-time faller, multiple faller) will be assessed using Pearson’s chi-square statistics.

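### The falls hypothesis is about rates, but the only falls test named compares category proportions, uses no observation time and gives up power

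*Protocol article*

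**What the plan says.** All references are to the protocol article.

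- **Hypothesis (Data analysis):** "We hypothesize that benefits of the walking program will include decreased fall rates". Balance, endurance, strength, mood and other outcomes follow in the same list.
- **Falls method (Data analysis):** "Proportions of participants in the number of fall categories (e.g., non-faller, one-time faller, multiple faller) will be assessed using" Pearson's chi-square. No other falls analysis is named. The random-effects regression in the same section is described for the five measurement occasions, with no count or rate form.
- **Falls window (Other data collection):** falls are collected prospectively "for the period of the intervention (four months) and for four months following intervention", so over eight months. Facility clinical staff record them and research assistants copy the records.
- **Attrition (Sample size):** "We will collect data from an additional 50 participants in order to account for attrition". Morbidity and mortality are mentioned as further causes, without a figure.
- **Promise (Abstract, Methods/design):** analyses "taking into account both the longitudinal nature of the data and the potential for missing data points due to attrition".
- **Baseline fall risk (Procedures):** a physiotherapist will "assign a visual analogue risk score ranging from negligible fall risk to highest fall risk". The Data analysis section gives this score no role.

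**The concern.** A fall rate is falls divided by time observed. A chi-square on the shares of non-fallers, one-time fallers and multiple fallers contains no time, so it cannot estimate the quantity in the hypothesis. It also treats two falls and ten falls alike, ignores the order of the categories, and for three arms by three categories spends (3-1)(3-1) = 4 degrees of freedom on an overall test with no direction.

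Two things are at stake. A real reduction in falls is more likely to be missed, and whatever the test shows, neither benefit nor harm is quantified. For a walking programme in frail residents, falls bear on safety as well as efficacy. In addition, if falls observation time differed strongly between arms, the test could show a difference where none exists.

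**Working it through.** **1. What the document supplies.** The 129 participants are calculated for the repeated measures analyses with a standardised effect of 0.40. No fall rate, dispersion or falls effect is given, so there is no falls figure to reproduce. With the extra 50, enrolment is 129 + 50 = 179, or 179/3 = about 60 per arm, and the allowance is 50/179 = 27.9%. The allowance is already inside the 179. Calculations should therefore use 60 per arm with loss, or 43 per arm without it; 43 per arm with 28% loss would remove attrition twice.

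**2. Assumed inputs.** Fall rate r between 1.0 and 2.5 per person-year, negative binomial counts with dispersion 1, eight months of observation, and leaving times uniform over that period and unrelated to fall risk. These are illustrations, not trial figures.

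**3. Why time matters.** Over t months the mean count is m = r × t/12, and the chance of no recorded fall is 1/(1 + m).
- r = 2, t = 8: m = 1.333, so 1/2.333 = 43%.
- r = 2, t = 2: m = 0.333, so 1/1.333 = 75%.

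For someone leaving at a uniform time the chance is ln(1 + m)/m = 0.847/1.333 = 64%. The expected non-faller share with no treatment effect is then:
- 15% leaving: 0.85 × 0.429 + 0.15 × 0.636 = 46%.
- 45% leaving: 0.55 × 0.429 + 0.45 × 0.636 = 52%.

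This applies only if leavers stay in the table and their falls are no longer captured.

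**4. Why collapsing matters.** At m = 1.333, the chance of two or more falls is (m/(1 + m))² = 0.571² = 33%, and of three or more 0.571³ = 19%. So 19/33, or 57%, of multiple fallers have three or more falls, and the test does not use that information.

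**5. Power (simulated).** The walking arm has the stated rate ratio and the other two arms share one rate. The chi-square (4 df) is compared with a negative binomial model with log person-time offset. Ranges cover separate sets of runs, with the dispersion either known or estimated.

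| Setting | Chi-square | Rate model |
|---|---|---|
| Rate ratio 0.5, 59-60 per arm, 28% loss, 1.5-1.6 falls/year | 40-43% | 63-66% |
| Rate ratio 0.5, 59-60 per arm, 28% loss, 2.5 falls/year | 46-47% | 75-76% |
| Rate ratio 0.6, 2 falls/year | 25% | 46% |
| Rate ratio 0.7, 59-60 per arm, 28% loss | 14-15% | 20-28% |
| Rate ratio 0.5, 43 per arm, no loss | 37-40% | 62-63% |

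The last row shows that the gap does not depend on attrition. In the 59-per-arm runs the rate model also recovered the effect: median estimates were 0.50 for a true 0.5 and 0.69-0.71 for a true 0.7.

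**6. False positives (simulated, no true effect, nominal 5%).**

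| Loss by arm, walking last | Chi-square |
|---|---|
| 28/28/28% | about 4-6% |
| 20/20/30% | about 4-5% |
| 20/20/44% | 5.9-6.9% |
| 15/15/45% | about 8-10% |
| 14/14/56% | 9.4-12.7% |

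The rate model stayed at 4.3-6.3% in the equal, 20/20/44% and 14/14/56% settings. With 1,000 trials per cell the standard error near 5% is √(0.05 × 0.95/1000) = 0.7 points, so the equal-loss results do not differ from nominal.

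**The case against.** **Bias.** A reader might infer that every early leaver is counted as a non-faller and that the test is therefore biased in favour of walking. The article does not support that. It does not say how leavers are classified, and the mechanism could touch only those who leave before a recorded fall. Falls come from routine facility records, so a resident who stops the programme but stays in the facility may still be observed. The 28% allowance need not be 28% lost falls time. Nothing in the article predicts markedly higher loss in the walking arm, and eligibility requires willingness to walk five days a week. This stands: with equal or modestly unequal loss the test keeps its level.

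**Over-reading.** The categories are given as examples, so the cut-points are not fixed. An article condenses a longer plan, and nothing excludes a further falls analysis. This stands in part. Days at risk, reporting by period and covariates are details that such a plan may hold. The choice of test is different: the article states one, and that one does not match its own hypothesis.

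**Weight.** No primary outcome is designated, falls are described under Other data collection and not in the numbered outcome list, and the sample size was not set for falls. This stands and limits the severity.

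**The alternative.** The offset model assumes that leaving is unrelated to fall risk given the covariates. That is doubtful when residents leave through decline or death, and the simulations build it in. Excluding leavers is no better, because it discards observed falls and selects survivors.

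**Conclusion.** The point holds as a mismatch between hypothesis and test, with a material loss of power. At a rate ratio of 0.5 the chi-square gives up roughly 20 to 30 percentage points of power against a rate model. At 0.7 the gap is smaller, and neither method has useful power at this sample size. These sizes rest on assumed fall rates and dispersion; the direction held in every setting tried. Naming a test without observation time also sits badly with the abstract's promise about attrition.

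Bias is a conditional risk, not an established fault, because it needs falls observation time that differs strongly between arms. It would also be too strong to say that a fall rate will never be estimated: the article names no such analysis, but a fuller plan might. Severity: should be fixed.

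**What to change.** Make the falls analysis a negative binomial (or overdispersed Poisson) regression of fall counts, with log(days observed) as offset and with group and facility as covariates, since randomisation is within facility. Report rate ratios with confidence intervals for walking versus usual care and walking versus interaction. State how residents who leave early contribute, and whether facility falls records are still collected after they stop the intervention. Keep the category table as description.

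Adjusting for the physiotherapist's baseline fall-risk score and reporting months 0-4 and 4-8 separately are optional refinements.

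The cost is analysis wording plus deriving days at risk from charted dates of death, transfer, hospitalisation and withdrawal. Falls records and hospitalisations are already collected. Because the model relies on leaving being unrelated to fall risk given the covariates, time observed and reasons for leaving should be shown by arm.

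### The falls hypothesis is about rates, but the only falls-specific test uses none/one/multiple categories that take no account of how long each resident was observed

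*Protocol article*

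**What the plan says.** The Data analysis section of the protocol article states the falls hypothesis in terms of rates: "We hypothesize that benefits of the walking program will include decreased fall rates". The same section gives falls one method of their own: "Proportions of participants in the number of fall categories (e.g., non-faller, one-time faller, multiple faller) will be assessed" by Pearson's chi-square. The random-effects regression described just before is built on the five measurement occasions. It does not mention falls and has no count distribution or exposure term.

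Under Other data collection, falls come from the health region's fall documentation, "for the period of the intervention (four months) and for four months following intervention", so eight months in all. Clinical staff make the records and research assistants copy them.

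On losses, the Sample size section adds "an additional 50 participants in order to account for attrition due to refusal or inability to continue with the protocol" to the 129 required, and notes that "morbidity and mortality may account for some attrition". The abstract describes the analysis as "taking into account both the longitudinal nature of the data and the potential for missing data points due to attrition".

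**The concern.** A fall rate is falls per unit of time at risk. A table of residents with none, one or several falls has no time in it, so the stated test does not address the stated hypothesis unless everyone is observed for about the same time. The plan expects some residents to be lost, and the falls test is the one analysis where the promised allowance for attrition is visibly absent.

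If residents with partial follow-up are kept in the table, someone who dies fall-free in the first month is classed with someone fall-free for eight months. Should the walking arm be observed for less time, it would gain non-fallers and lose multiple fallers without any true effect. Should the control arms be observed for less time, a real benefit would be partly hidden.

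Unequal loss is plausible in either direction. Only the walking arm must walk five days a week for four months, which could raise its losses; if walking protected against illness, losses could be higher in the controls.

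**Working it through.** **Inputs from the article.** Falls follow-up is 4 + 4 = 8 months. Planned total is 129 + 50 = 179, so the attrition allowance is 50/179 = 27.9%, with no split by arm. Equal groups give 179/3, about 60 per arm. The article states no fall rate and no power for falls, so there is no falls figure of its own to reproduce.

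**Assumptions.** 1.5 falls per person-year (0.125 per month), the same in every arm. Gamma frailty with variance 1. Residents who leave do so uniformly over the 8 months, regardless of fall risk, and stay in the table with the falls seen so far.

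**Step 1: chance of each category.** With μ = 0.125 × (months observed):
- P(no fall) = 1/(1 + μ). At 8 months μ = 1, giving 0.500. Averaged over uniform exit, it is ln 2 = 0.693.
- P(two or more) = (μ/(1 + μ))². At 8 months this is 0.250. Averaged over uniform exit, it is 1 − 2 ln 2 + 0.5 = 0.114.

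**Step 2: equal true rates, observation cut short in 20% (usual care) versus 40% (walking).**
- Non-fallers, usual care: 0.8 × 0.500 + 0.2 × 0.693 = 53.9%.
- Non-fallers, walking: 0.6 × 0.500 + 0.4 × 0.693 = 57.7%.
- Multiple fallers: 0.8 × 0.250 + 0.2 × 0.114 = 22.3% versus 0.6 × 0.250 + 0.4 × 0.114 = 19.5%.

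The spurious gap in non-fallers is (0.40 − 0.20) × (0.693 − 0.500) = 0.20 × 0.193 = 3.9 points.

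**Step 3: scale.** Under full observation, a true rate ratio of 0.7 would give 1/(1 + 0.7) = 58.8% non-fallers against 50.0%, a gap of 8.8 points. The spurious gap is 3.9/8.8 = 44% of that. It is also only about 0.4 standard errors: √(2 × 0.558 × 0.442/60) = 9.1 points.

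**Step 4: if only half of the loss truncates falls records** (10% versus 20%): 0.10 × 0.193 = 1.9 points.

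**Step 5: range over assumptions.** Exact category probabilities and the non-central chi-square, 60 per arm, equal true rates, 1.0 to 2.5 falls per person-year, Poisson or negative binomial with dispersion 1, two-arm or three-arm test. Each split averages 28% over the three arms, with both controls at the lower figure where loss is unequal.

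| Truncated: one arm vs the others | Excess non-fallers | False-positive rate |
|---|---|---|
| 28% vs 28% | 0 | 5.0% |
| 36% vs 24% | 2.0 to 3.6 points | 5.4% to 6.7% |
| 42% vs 21% | 3.5 to 6.3 points | 6.2% to 10.4% |
| 54% vs 15% | 6.5 to 11.6 points | 9.3% to 25.3% |

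A separate simulation of the pairwise chi-square (4,000 trials per scenario, 1.5 and 3 falls per person-year) gave 4.0% to 5.4% at equal loss, 6.6% to 6.8% at 40% versus 20%, and 9.8% to 11.7% at 49% versus 15%.

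**Step 6: the same kind of data with observed time as offset.** In simulated three-arm trials at 1.5 falls per person-year with dispersion 1, robust Poisson regression with the offset gave a rate ratio for walking against the pooled controls of 0.98 (42% vs 21%) and 0.99 (54% vs 15%). Without the offset it was 0.86 and 0.78. Over all the simulations run, the offset model rejected in 5.5% to 6.8% of trials. The absence of bias here follows from simulating exit as unrelated to fall risk.

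**The case against.** The strongest reply is that the attrition allowance is not shown to be lost falls observation. A reader might infer that 28% of residents will have truncated falls data. The article does not say so: the extra 50 cover refusal or inability to continue with the protocol, and falls are documented by clinical staff whether or not a resident attends sessions. Someone who stops walking may still be observed for falls. Death ends observation; for transfer and withdrawal the article is silent. This stands, and makes 28% an upper guide only.

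Second, the bias between arms needs unequal observed time, and the article neither gives nor predicts a split. This also stands. At a moderate split the chi-square's error rate overlaps that of the offset model, so the gain there is in the estimate more than in the test.

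Third, a reader might infer that every category analysis has this fault. That is too strong. The article states no rule on who enters the table; restricting it to residents with full follow-up would avoid this mechanism, at the price of selection.

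Fourth, a reader might infer that the falls window has no defined start in usual care because that arm has no sessions. The Intervention section contradicts this by giving the control group the same four-month period.

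Finally, falls are named first among the hypothesised benefits but are not in the numbered outcome list, and no primary outcome is declared, so the point should not be read as undermining the trial's main result. An unseen analysis plan might add an exposure-adjusted analysis. The article nevertheless fixes the chi-square itself, so this is a stated method that fits its hypothesis badly, not an omitted detail.

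**Conclusion.** The point holds in conditional form. The article states a rate hypothesis and tests it with categories that ignore observed time, while expecting attrition and promising to allow for it. If observed time differs between arms and partial follow-up stays in the table, the arm with less observation looks better even at equal true rates.

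The size rests on assumptions that the documents cannot settle: about 3.9 points in non-fallers at 20% versus 40% truncation, about 1.9 points if half of that loss affects falls records, and nothing at equal loss. False-positive inflation is roughly 6% to 10% at a twofold imbalance and becomes marked only at a much larger one. The main harm is a misleading estimate. The change should be made, since the replacement is cheap and matches the hypothesis as written.

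**What to change.** Test the falls hypothesis with a negative binomial model, or Poisson with robust standard errors, on each resident's fall count, allowing for facility. Use as offset the log of days at risk: from the start of the four-month period, defined alike in all three arms, to month 8, death, transfer out of the facility or withdrawal from data collection, less days in hospital. Report rate ratios with confidence intervals for walking against each control. Keep the three fall categories as description, shown with time observed by arm. State whether falls records continue to be copied after a resident stops sessions.

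The cost is wording plus exit dates. Falls and hospitalisations are already collected from the charts, but the article does not say that dates of death, transfer and withdrawal are captured, so these must be recorded for each resident. No extra visits or residents are needed.

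The offset does not remove bias from dropout related to fall risk, which is likely where illness or death is the cause. Add a sensitivity analysis, for example imputing the unobserved falls at a range of higher rates after exit among residents who leave alive.
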